### Statistical analysis

Following the intention-to-treat approach we will include all randomized participants in the primary analyses in order to avoid biases such as non-random attrition of participants. As many of the randomized participants decline to take part in the TBHC we run a second intention-to-treat approach, testing the participants versus the control group. Additionally we will perform a sensitivity analysis following the as-treated approach including only participants that have received a minimum of five coaching calls.

Therefore, three different analyses will be performed:

- 1) Intention-to-treat 1: comparing the randomized intervention group (including decliners) versus the control group.
- 2) Intention-to-treat 2: comparing those who took part in the intervention versus the control group (excluding the decliners).
- 3) As-treated: comparing participants who received a minimum of five calls versus the control group.

In order to enhance the comparability of intervention group and control group in the health economic outcomes for analyses 2 and 3, propensity score matching (PSM) will be used to control potential confounding. Routine data from the 12-month period preceding recruitment will be used to match individuals in the intervention group with controls by means of propensity scores. Formally, the propensity score is a person's probability of being assigned to the intervention group given a set of observed covariates. The covariates in the propensity score model will be based on routine data: for example, age, sex, ICD diagnoses, number of days spent in hospital and healthcare costs in the preceding year. The predicted probabilities of unconditional logistic regression models with 'treatment' (intervention versus controls) as dependent variable and the described set of covariates are the basis for the subsequent matching of both groups.

For the primary outcome 'time until hospital readmission' we will use the hazard ratio from a proportional hazard model. Service use and costs will be analyzed by logistic and linear random effects regression models using bootstrapped standard errors.

The secondary outcomes that are patient reported will include different scales, instruments and items with various scale levels. For the analyses of nominal scaled outcomes we will use chi-square tests. Ordinal and interval scaled outcomes will be analyzed using ANOVA

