### Treatment allocation

To ensure comparability between the intervention and the control group, a stratified random allocation design will be used based on sociodemographic values with a 5:1 allocation ratio to intervention and control group. The randomized intervention group consists of participants and decliners. The decliners will not receive any TBHC. However, they will have the opportunity to opt in to the TBHC via a telephone number printed on the questionnaires. In that case, they will be excluded from the study.

Once the patients are assigned to one of the three groups there will be no blinding of coaches, patients or researchers and their assistants. Nevertheless, the coaches will not know who is responding in the study. The questionnaires are pseudonymized.

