### Power calculation

Calculation of the target sample size was based on the patient reported outcomes collected by questionnaire. In order to achieve a power of at least 95% at a type I error rate of  $\alpha = 5\%$  in a two-sided test accounting for the unbalanced group allocation, a minimum of 1,670 patients are needed to be able to detect a small standardized mean difference in group comparisons (Cohen's  $d$  of 0.2) [28] at  $T_2$  following the intention-to-treat principle. Assuming a response rate between 18% and 40% and drop-out rates between 10% and 82% depending on group and phase, a target sample size of approximately 9,000 patients was identified who should be invited to the questionnaire survey. Assuming that around 65% of the invited patients will decline participation and half of them will be followed up, a total of 12,000 patients were targeted (see Figure 1). Because the primary outcome 'time until hospital readmission' is collected from routine data available for the total sample of 12,000 patients from the KKH statutory health insurance, the primary analysis is sufficiently powered to detect even very small effects with a high probability (low type II error).

[figure not shown]

**Figure 1** Expected participant flow for patient-reported outcomes.

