## Discussion

This study is a 4-year RCT that examines the economic and psychosocial evaluation of a telephone-based health coaching. The evaluated intervention is a health coaching delivered by phone by specially trained nurses. It focuses on lifestyle change using motivational interviewing techniques combined with individual goal setting. The coaching is manualized and computer supported.

As there are just few publications about the health economic evaluation of telephone-based health coaching (TBHC) programs, and especially few about TBHC in the German healthcare system, this trial can fill the existing gap. Our findings will be relevant for future health coaching programs as potential cost savings are interesting for statutory health insurances.

Nevertheless, there are some limitations to this study: Randomization took place before informed consent was obtained from participants. As participants and decliners are likely to be different, this may cause bias with respect to the groups compared in the intention-to-treat-2 and the as-treated analysis. Although we apply advanced statistical methods, potential confounding cannot be ruled out completely. Another limitation could be the unsure validity of the routine data, but an extensive literature research revealed that the quality of routine data in Germany is good [29]. The generalizability of the secondary patient reported outcomes may be limited by social desirability, because the statutory health insurance is sending out the questionnaires. To prevent this bias we assured the insurants in the cover letter that non-response will definitely have no negative consequences. Another possible limitation is the quality of the items questioning the clinical parameters like HbA1c. They are patient reported on an ordinal scale, which means they are prone to be inexact. To approach this problem we take advantage of the opportunity to use the software data available for the participant group as well.

Since the amount of studies evaluating psychological and economic outcomes of health coaching interventions are rare, our study will provide evidence, which is needed for different healthcare bodies. The study's outcome will

help determine whether TBHC is a promising tool to enhance the self-management of chronically ill patients and thus reduce costs, increase quality of life and change clinical parameters.

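### 'Intention-to-treat 2' drops the roughly 65% of the intervention arm who decline; it is a non-randomized comparison and should be renamed, ranked below ITT-1 and backed by a randomization-based estimate

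*Protocol*

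**What the plan says.** The protocol's Statistical analysis section puts all randomized patients into the primary analyses and lists three comparisons. The first is "Intention-to-treat 1: comparing the randomized intervention group (including decliners) versus the control group". The second is introduced with the words "we run a second intention-to-treat approach, testing the participants versus the control group" and listed as "Intention-to-treat 2: comparing those who took part in the intervention versus the control group (excluding the decliners". The third, as-treated, requires at least five calls. Only the third is called a sensitivity analysis.

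Matching on propensity scores built from prior-year routine data is planned "In order to enhance the comparability of intervention group and control group in the health economic outcomes for analyses 2 and 3". For patient-reported outcomes the section names ANOVA and ANCOVA, with covariate adjustment if the groups differ significantly.

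Randomization comes before invitation and consent, "with a 5:1 allocation ratio to intervention and control group" (Treatment allocation). Controls are not invited and receive no coaching (Study procedures; Control condition). The expected uptake is in Power calculation: "Assuming that around 65% of the invited patients will decline participation and half of them will be followed up". The Discussion expects participants and decliners to differ and says "this may cause bias with respect to the groups compared in the intention-to-treat-2 and the as-treated analysis".

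**The concern.** Intention-to-treat keeps each patient in the arm assigned by randomization. Analysis 2 selects on a choice made after randomization, and in one arm only. The control arm is a mixture of people who would have accepted coaching and people who would have declined; the retained part of the intervention arm contains acceptors only. If the two types differ in prognosis, the comparison shows a difference even when coaching does nothing.

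The section gives the intention-to-treat name to two analyses of very different validity, and only the words about the primary analyses rank one above the other. The planned safeguard is partial in three ways:

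- Matching can balance only covariates found in routine data, and Primary outcome says those data hold no clinical parameters.
- It is unclear whether matching covers the readmission outcome. Secondary outcomes speaks of further economic evaluation, which suggests that readmission counts as economic, but nothing says so.
- For patient-reported outcomes, adjustment depends on a significance test, which is weak protection.

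**Working it through.** **1. What the 65% refers to.** Inputs are 12,000 patients, 5:1 allocation, 65% declining, half of the decliners surveyed, and about 9,000 invited to the survey (Treatment allocation; Power calculation).

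- Intervention: 12,000 × 5/6 = 10,000. Control: 2,000.
- Decliners: 0.65 × 10,000 = 6,500. Participants: 3,500.
- Invited to the survey: 2,000 + 3,500 + 6,500/2 = 8,750, within 3% of the stated 9,000.
- Taking 65% of all 12,000 instead gives 12,000 − 7,800/2 = 8,100, which does not fit. The 65% is therefore a share of the intervention arm.

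**2. What analysis 2 keeps.** It keeps 3,500 + 2,000 = 5,500 of 12,000 patients, or 46%. The ratio becomes 1.75:1 instead of 5:1.

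**3. Bias when coaching has no effect, unmatched and unadjusted.** Let rr be the underlying participant/decliner hazard ratio. The protocol gives no value, so the range is an assumption. Controls average 0.35 × rr + 0.65 relative to decliners, so analysis 2 shows approximately

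HR = rr / (0.35 rr + 0.65) = 1 / (0.35 + 0.65/rr).

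The standard error is 1/√(5,500 × event share × 0.636 × 0.364), which is 0.0396 with 50% events and 0.0348 with 65% (event shares assumed). Two-sided type I error at alpha 5% comes from a normal shift of ln(HR)/SE.

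| rr | Spurious HR | Shift, 50% / 65% events | Type I error |
|---|---|---|---|
| 0.95 | 0.967 | 0.85 / 0.97 | 14-16% |
| 0.90 | 0.933 | 1.76 / 2.01 | 42-52% |
| 0.80 | 0.860 | 3.80 / 4.33 | 97-99% |

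Selection can run the other way. With decliners at 0.9 or 0.8 times the participants' hazard, the spurious HR is 1/(0.35 + 0.65 × 0.9) = 1.07 or 1/(0.35 + 0.65 × 0.8) = 1.15.

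**4. Patient-reported outcomes.** The unadjusted bias is 0.65 × the participant-decliner difference. An assumed difference of 0.10 or 0.20 SD gives 0.065 or 0.13 SD, against the 0.2 SD that the survey is sized to detect.

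**5. A randomization-based alternative.** Controls are not coached, so non-adherence is one-sided, and routine data cover the whole randomized sample. Assume a control readmission risk of 0.50 and a decliner/participant risk ratio of 1.2. Untreated participant risk is then 0.50/(0.35 + 0.65 × 1.2) = 0.4425.

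- True effect 0: analysis 2 gives 0.4425 − 0.50 = −0.058. The ITT-1 difference is 0, and 0/0.35 = 0.
- True effect −0.05 in participants: analysis 2 gives about −0.108. The ITT-1 difference is 0.35 × (−0.05) = −0.0175, and −0.0175/0.35 = −0.05.

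A simulation of 4,000 trials under these values agreed: analysis 2 averaged −0.058 and −0.108, the complier estimate −0.000 and −0.050. Standard deviations were about 0.012 for ITT-1, 0.014 for analysis 2 and 0.034 to 0.035 for the complier estimate.

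**The case against.** The best defence is that ITT-1 is the primary analysis and keeps everyone, that the Discussion names the selection problem openly, and that analyses 2 and 3 are extras with matching attached. Most of this stands. A reader might infer that the trial's main result is compromised, that the selection is hidden, or that analysis 2 will be presented as equal to ITT-1. The protocol supports none of these.

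The error rates also invite over-reading. They describe an unadjusted analysis at alpha 5%. If readmission counts as a health economic outcome, matching on prior hospital days, costs, diagnoses, age and sex would remove part of the bias. A Bonferroni correction is planned, though its family is not defined. Over the three analyses (alpha 0.0167) the 42-52% would become about 26-35%. Nor can one infer that the bias favours coaching, since its direction is unknown.

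Two further inferences fail. The group sizes might suggest that matching must discard many participants, but the protocol fixes neither a matching ratio nor a replacement rule. And patient-reported outcomes are not wholly unadjusted, because conditional covariate adjustment is planned.

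Finally, the lack of a complier analysis is not in itself an error, since a statistical analysis plan could supply one. What the defence does not rescue is the name, or the missing statement that analysis 2 is supportive.

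**Conclusion.** Analysis 2 is mislabelled. It excludes about 6,500 of 10,000 intervention patients on a post-randomization choice and compares volunteers with an unselected control group. The protocol itself expects the two types to differ, calls the comparison intention-to-treat all the same, and does not give it the sensitivity status that it gives the as-treated analysis. ITT-1 is not affected by this point.

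The bias follows from the design whenever participants and decliners differ in prognosis. Its size is not known. The tabulated rates rest on assumed hazard ratios and event shares, no coaching effect, no matching or adjustment, and alpha 5%. Matching or a stricter alpha would lower them. They show that even a modest difference is enough to mislead at these sample sizes; they do not forecast the planned analysis.

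**What to change.** - Rename analysis 2 'participants versus controls (non-randomized comparison)'. Mark it and analysis 3 as supportive, and state that conclusions rest on ITT-1. A per-protocol label would not suit, because participants are defined by returning a confirmation, with no minimum number of calls.
- State whether matching covers the readmission outcome.
- For routine-data outcomes, add a complier average causal effect on a difference scale (24-month readmission risk, restricted mean time to readmission, costs). This is the ITT-1 difference divided by the proportion of the intervention arm coached, with a bootstrap interval. It must not be applied to the hazard ratio.
- State its assumption that the invitation and acquisition call have no effect of their own.
- Change Treatment allocation, which removes decliners who opt in later, so that they stay in the analysis and count as coached.
- If the estimate is extended to patient-reported outcomes, weight the surveyed half of the decliners by two and handle non-response.

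The cost is wording and one extra analysis; routine-data outcomes need no new data. The downside is precision: the interval is about 1/0.35 = 2.9 times as wide as for ITT-1.

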## Methods/Design

### Study design

The study is a prospective randomized controlled trial (RCT) comparing TBHC with patients in usual care during a 4-year time period. There are three follow-up measures; in addition to the baseline measure ( $T_0$ ) the data will be assessed again at 12 months ( $T_1$ ), 24 months ( $T_2$ ) and 36 months ( $T_3$ ). The length of the coaching will be tailored to the needs of the patient, but will not exceed two years.

The studies comply with the Helsinki Declaration 2008. The ethics approval was granted by the Hamburg Medical Chamber Ethics Committee.

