### Sample procedures

#### Inclusion criteria for patients

Participants should be at least 18 years old and insured of the KKH statutory health insurance. Moreover, included patients will need to have one or more diagnoses of the following: diabetes, coronary artery disease, asthma, hypertension, heart failure, chronic obstructive pulmonary disease (COPD), chronic depression or schizophrenia. Additional inclusion criteria will be used for each target disease. For example, for patients with type 2 diabetes, hypertension or coronary artery diseases, a risk score for hospital readmission will be calculated. Based on various variables from routine data a logistic regression model was designed to predict hospital readmission using SPSS 19. Those variables are, for example, healthcare costs, international classification of diseases (ICD)-diagnoses, age and gender. This model has been validated by analyzing the receiver operating characteristic curve (ROC) [26] and the positive predictive value [27] and showed valid predictions. If the calculated risk for hospital readmission within the next year is higher than 50%, the person will be included in the study. Patients will be excluded from the study if they have insufficient German language skills, are hard of hearing or are not able to read or use a phone.

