## Description of the intervention and control condition

### Intervention condition

The TBHC will follow the concepts of motivational interviewing techniques, individual, collaborative goal setting and shared decision-making. The coach will lead the conversation, but will try to follow a non-directive approach. There will be a minimum frequency defined as one telephone contact every six weeks. The TBHC will have a maximum duration of two years. The intervention will be tailored to chronic diseases that are in need of similar self-management strategies: 1) asthma and COPD, 2) type 2 diabetes, hypertension and coronary artery disease, 3) heart failure and 4) depression and schizophrenia. Each of these disease-specific implementations of the TBHC intervention will have its own treatment manual. These manuals will include information about the inclusion criteria, the scientific background of the campaign and its key contents. All components of the campaign such as the coaching process will be described as well. For example, there will be instructions for specific coaching situations and main topics (for example, diet, immunization and foot control in diabetes and complementary medicine). Even though these instructions exist, the coaching will be tailored to the patients' needs and his individual medical condition. Additionally, the coaches will be supported by a web library and a software program. The web library will provide health information to the coaches to ensure that the information given is evidence-based and up-to-date (for example, by referring to actual

clinical practice guidelines). The software contains available printed information material such as education leaflets for specific conditions, medication plans and weight-control tables that can be sent to the participants by mail. The software also offers a tool to document the process, individual goals, medication, clinical parameters (like HbA1c or blood pressure) and diagnoses.

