### Outcome assessment

#### Primary outcome

The primary outcome is the time from enrollment until hospital readmission within two years. Time until

hospital readmission will be assessed using routine health insurance data of the KKH that records the date of enrollment in the study as well as the dates of hospital stay.

The routine data will be collected and provided by the statutory health insurance. They are generated during the everyday healthcare business and show the actual healthcare situation of the insurant. Every contact within the healthcare system is represented: doctor and hospital visits with ICD code and Operationen- und Prozedurenschlüssel (OPS) code, the German equivalent to the American procedure coding system (PCS), incapacity to work, the medication and much more. The data are not influenced by non-response or recall-bias as they are assessed directly at the healthcare provider. Routine data depicts accountable variables, but not clinical parameters. The validity of routine data in Germany is not proven, yet studies show that the ICD diagnoses are valid in about 97% for heart failure [29,30]. The routine data are read out by the KKH and securely delivered with pseudonymized codes. The outcomes based on routine data include data of the whole randomized sample of approximately 12,000 insurants.

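### The as-treated analysis selects on five calls reached after enrolment but counts time from enrolment: immortal-time bias for mortality, a likely selection bias for readmission

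*Protocol*

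**What the plan says.** The Protocol, Statistical analysis, lists three comparisons. The third is "As-treated: comparing participants who received a minimum of five calls versus the control group", and the same section gives its role: "Additionally we will perform a sensitivity analysis following the as-treated approach including only participants that have received a minimum of five coaching calls".

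The clock is set under Primary outcome: "The primary outcome is the time from enrollment until hospital readmission within two years". For that outcome, "we will use the hazard ratio from a proportional hazard model". No landmark, delayed entry or time-dependent exposure is mentioned.

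The pace and length of coaching are given elsewhere. Intervention condition: "There will be a minimum frequency defined as one telephone contact every six weeks". Study design: "The length of the coaching will be tailored to the needs of the patient, but will not exceed two years". Nothing says that a readmission ends coaching.

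For the second and third comparisons the Protocol adds propensity score matching, stated for the health economic outcomes: "Routine data from the 12-month period preceding recruitment will be used to match individuals in the intervention group with controls". Mortality is listed under Secondary outcomes among the health economic measures. The Discussion concedes possible bias in the as-treated comparison, but only because participants and decliners are likely to differ.

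**The concern.** Membership of the coached group depends on something that happens during follow-up. A participant who dies before the fifth call can never enter the group, and one who is admitted and then stops does not enter it either. A control with the same early event stays in and is counted. The time between enrolment and the fifth call is therefore partly or wholly protected in one group and not in the other.

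The Protocol presents this as a sensitivity analysis, and about 65% of those invited are expected to decline. Readers will therefore look to the five-call result for the effect of coaching actually received. A stronger result there than in the intention-to-treat comparison could look like a dose-response when it is only selection.

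**Working it through.** The Protocol gives no figure for this comparison, so there is none to reproduce. The check asks what hazard ratio the stated rule returns when coaching has no effect.

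**Inputs from the Protocol.** At least five calls; at least one call every six weeks; time from enrolment; two-year horizon; proportional hazards model; and a risk threshold, "If the calculated risk for hospital readmission within the next year is higher than 50%, the person will be included in the study". That threshold is given as an example for type 2 diabetes, hypertension and coronary artery disease.

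**Assumptions.** Constant hazards; one-year readmission risk 50% (also 20%); annual death risk 4%; and q, the share of participants readmitted before the fifth-call time who then stop before call five. The Protocol gives no value for q, so it runs from 0 to 1.

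**Time to the fifth call.** At the minimum frequency it is (5 − 1) × 6 = 24 weeks if the first call is at week 0, or 5 × 6 = 30 weeks if it is at week 6. Because six weeks is a minimum frequency, these are the slowest permitted times. Week 12 is used as a faster example.

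**Readmissions before that time, 50% one-year risk.** 1 − 0.5^(24/52.18) = 0.27 and 1 − 0.5^(30/52.18) = 0.33.

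**Null hazard ratio, readmission.** Let λ = −ln(1 − one-year risk), T the fifth-call time, and S0 = e^(−λt) and f0 = λS0 for controls. In the coached group the event density is (1 − q)f0 before T and f0 after. The number at risk is S1 = e^(−λT) + (1 − q)(e^(−λt) − e^(−λT)) before T and S0 after. The large-sample Cox estimate θ solves ∫[f1 − (f1 + f0)·θS1/(θS1 + S0)]dt = 0 over two years, with equal groups before selection.

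| One-year risk, fifth call | q = 0 | 0.10 | 0.25 | 0.50 | 1 |
|---|---|---|---|---|---|
| 50%, week 24 | 1.000 | 0.969 | 0.921 | 0.838 | 0.660 |
| 50%, week 30 | 1.000 | 0.964 | 0.908 | 0.810 | 0.595 |
| 50%, week 12 | 1.000 | 0.982 | 0.954 | 0.907 | 0.811 |
| 20%, week 24 | 1.000 | 0.974 | 0.935 | 0.869 | 0.735 |

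A simulation with 200,000 per group before selection agrees to about 0.01.

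**Null hazard ratio, mortality.** Here q = 1 by definition. When deaths are few, the numbers at risk are almost equal, so the ratio is close to the share of follow-up in which coached deaths can be counted, (104 − T)/104 with T in weeks:

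- week 24: 80/104 = 0.77
- week 30: 74/104 = 0.71
- week 12: 92/104 = 0.88

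The equation above with a 4% annual death risk gives 0.764, 0.706 and 0.881. The Protocol names no model for mortality, so the hazard-ratio scale is a choice made here.

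**Check of the remedy.** In the same readmission simulation, restricting both groups to those event-free at T and restarting the clock there gives 0.99 to 1.01 in every scenario.

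**Existing safeguards.** Matching uses only data from before recruitment, so it cannot balance events that occur after enrolment.

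**The case against.** The strongest objection is that readmission does not prevent a fifth call. A reader might infer that the analysis must favour coaching even when coaching does nothing. The documents do not support that for the primary outcome: no text says admission ends coaching, and if nobody stops the null hazard ratio is 1.00. The direction is not fixed either. Coaching length follows need, so if healthier participants finish before five calls, the retained group is sicker and the bias runs against coaching. This objection stands, and it limits the readmission claim to a likely bias of unknown size.

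A reader might also infer that five calls take half a year. That is only the slowest permitted pace.

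A third inference is that the artefact exceeds any effect the intention-to-treat comparison could detect. The Protocol gives no event-based power. Assuming 12,000 × 0.75 = 9,000 events and 5:1 allocation, the detectable hazard ratio is exp(−2.80/√(9,000 × 5/36)) = 0.92 at 80% power and exp(−3.24/√1,250) = 0.91 at 90%. The 10% scenario, at 0.96 to 0.97, does not reach that. Only around a quarter stopping does the artefact become comparable.

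It can also be said that this is only a sensitivity analysis, that the Discussion already warns of bias, and that a landmark is a matter for the SAP. The first lowers the severity. The warning concerns who agrees to take part, not time to the fifth call. On the SAP, the Protocol itself fixes the group definition, the clock and the model, and together these create the problem. If an SAP already specifies a landmark, the Protocol needs only to be aligned with it.

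**Conclusion.** The point holds in a limited form and should be fixed. For mortality the rule produces true immortal-time bias: a null hazard ratio of about 0.71 to 0.76 with the fifth call at week 24 to 30, and about 0.88 at week 12. These values depend little on the assumed 4% death risk, as the (104 − T)/104 approximation shows.

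For readmission the bias is likely, but its size rests on an unknown stopping share. At a 50% one-year risk and the slowest pace it runs from none to a hazard ratio of 0.59, and a reversal is possible. The 50% is an inclusion threshold for some of the diseases, not a known event rate for the whole sample.

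The Protocol does not name this bias and its matching cannot remove it. The primary comparison of all randomized patients is not affected. As it stands, the as-treated result cannot serve as a test of that comparison's robustness.

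**What to change.** For readmission and mortality, replace the as-treated comparison with a landmark analysis:

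- Fix one landmark time, measured from a start of follow-up defined the same way in both groups.
- Classify participants by the calls received by the landmark.
- Restrict both groups to people still at risk then: alive and insured and, for the readmission outcome, readmission-free.
- Count time from the landmark.

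Alternatively, enter five calls reached as a time-dependent covariate, so that time before the fifth call is not credited to coaching. In either case keep the baseline propensity adjustment, label the analysis exploratory, and do not present it as a check on the primary result.

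The cost is wording and modest programming. Call dates are needed; the Protocol says the coaching software documents the process, which should supply them but is not spelled out. A landmark at week 24 to 30 loses the patients with earlier events (about 27% to 33% at a 50% one-year risk) and does not estimate early effects. Participants who keep up with calls may still differ from controls in ways the baseline data do not capture, so some confounding remains.

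### The primary intention-to-treat hazard model is not stated to include the sociodemographic strata used in the allocation; if they are left out and are prognostic, some power is given away

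*Protocol*

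**What the plan says.** Under Treatment allocation, the protocol states that "a stratified random allocation design will be used based on sociodemographic values with a 5:1 allocation ratio to intervention and control group". It does not name the values, the number of strata or their cut-points.

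Under Primary outcome: "The primary outcome is the time from enrollment until hospital readmission within two years". This outcome comes from routine insurance data and covers "data of the whole randomized sample of approximately 12,000 insurants". At 5:1 that is about 10,000 against 2,000.

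Under Statistical analysis, the first intention-to-treat comparison (ITT-1) is described as "comparing the randomized intervention group (including decliners) versus the control group". The primary model gets one clause: "we will use the hazard ratio from a proportional hazard model". No strata or covariates are listed for it, and it is not called unadjusted or unstratified.

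Covariates appear in two other places in that section. Propensity score matching on routine data is limited to the health economic outcomes in analyses 2 and 3. An adjustment that depends on significant group differences stands in the text on patient-reported outcomes and uses logistic regression. Neither settles the primary model.

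**The concern.** Allocation within strata forces the arms to be alike on those strata. If the strata predict admission, this removes part of the chance variation in the estimated log hazard ratio. A proportional hazard model fitted without the strata does not register that gain. Its model-based standard error stays about where it was while the true sampling variation is smaller, so the test is more cautious than its nominal 5%. A model that carries the strata recovers the lost power and estimates the within-stratum hazard ratio.

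The strata may well be prognostic. The inclusion criteria name age and gender among the variables in the trial's own readmission model, and both are typical sociodemographic values. That the strata include them is an inference.

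Power near a hazard ratio of 1 matters here. The Power calculation section assumes that around 65% of invited patients decline, and ITT-1 keeps decliners in. If decliners have no effect, an overall hazard ratio of 0.915 corresponds very roughly to exp(ln 0.915 / 0.35) = 0.78 among participants. So a modest overall hazard ratio could reflect a sizeable coaching effect.

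**Working it through.** **The plan's own figures.** The protocol gives no hazard ratio, event count or power for the primary outcome, so there is nothing to reproduce. Its minimum of 1,670 concerns questionnaire outcomes and has no bearing here.

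**Inputs from the protocol.** About 12,000 randomised, 5:1, two years of follow-up. The two-sided 5% level is taken from the questionnaire power calculation.

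**Assumed inputs.** The strata and their prognostic strength, the event share and the true hazard ratio (HR).

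**Step 1: benchmark with strata in the model.** Take 60% events: 12,000 × 0.60 = 7,200. The standard error of the log HR is about 1/√(7,200 × 5/6 × 1/6) = 1/√1,000 = 0.0316. With HR 0.915, |ln HR| = 0.0888, so z = 0.0888/0.0316 = 2.81. Power is Φ(2.81 − 1.96) = Φ(0.85) = 0.80.

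**Step 2: the same trial without strata.** Four equal strata with hazards from 1 to 3 were simulated (3,000 trials, exponential times, censoring at 24 months). The model without strata gave HR 0.920, a mean model SE of 0.0318 and an empirical SD of 0.0298. Then:
- SE ratio: 0.0318/0.0298 = 1.07, so the model SE is 7% above the true variation.
- Mean z: |ln 0.920|/0.0318 = 0.0834/0.0318 = 2.62.
- SD of z: 0.0298/0.0318 = 0.937.
- Power: Φ((2.62 − 1.96)/0.937) = Φ(0.71) = 0.76, which agrees with the simulated 0.759.
- Null rejection rate at the same SD of z: 2 × (1 − Φ(1.96/0.937)) = 0.036, below 0.05.

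**Step 3: range of strengths.** Four strata, 60% events, HR 0.915. Where two pairs stand, they come from two separate simulations.

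| Largest/smallest stratum hazard | Power without v with strata | Loss (points) |
|---|---|---|
| 1.5 | 0.81 v 0.81 | 0 |
| 2 | 0.778 v 0.788; 0.78 v 0.80 | 1 to 2 |
| 3 | 0.759 v 0.804; 0.76 v 0.80 | 4 to 5 |
| 5 | 0.702 v 0.798; 0.74 v 0.81 | 7 to 10 |

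With 3,000 trials and power near 0.8, the simulation error of one figure is √(0.8 × 0.2/3,000) = 0.007.

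**Step 4: a different set-up.** Twelve equal strata, HR 0.90, 600 trials per row. The spread is the SD of the stratum log-hazard. For comparison, four strata spaced evenly on the log scale from 1 to 3 have SD (ln 3/3) × √1.25 = 0.41.

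| SD | Events | HR without v with | Model SE / empirical SE, without strata | Power without v with |
|---|---|---|---|---|
| 0.2 | about 70% | 0.900 v 0.898 | 0.0285/0.0287 | 0.958 v 0.957 |
| 0.4 | about 70% | 0.908 v 0.900 | 0.0286/0.0266 | 0.943 v 0.965 |
| 0.8 | about 70% | 0.923 v 0.901 | 0.0291/0.0249 | 0.812 v 0.935 |
| 0.4 | about 38% | 0.904 v 0.901 | 0.0388/0.0384 | 0.733 v 0.760 |

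At SD 0.4 the loss is 2 to 3 points; in the row with about 70% events, power is already close to its ceiling. The model SE with strata is 0.0285, 0.0286 and 0.0292 in the first three rows, almost the same as without.

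**Step 5: no effect (HR 1).** Without strata the HR stays at 1.00. The rejection rates are 0.060, 0.045 and 0.022 for SD 0.2, 0.4 and 0.8. With 600 trials the simulation error is √(0.05 × 0.95/600) = 0.009, so 0.060 is compatible with 0.05. The test turns conservative as the strata strengthen.

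**The case against.** The strongest objection is that silence is not a decision. A stratified Cox model is also a proportional hazard model, so "we will use the hazard ratio from a proportional hazard model" is compatible with "a stratified random allocation design will be used based on sociodemographic values". The list of strata and covariates in such a model is often left to a statistical analysis plan, and that plan is not at hand. This stands: the protocol contains no contradiction here, and the consequences can only be stated conditionally.

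A second objection is that the size is unknown because the strata are unnamed, and the strong scenarios fit poorly with the only risk figure in the protocol: "If the calculated risk for hospital readmission within the next year is higher than 50%, the person will be included in the study". Starting from a one-year risk of 50%, a fivefold hazard would mean 1 − 0.5^5 = 97%. Selecting on a score that uses age and gender also narrows the prognostic spread those variables can show. This largely stands. However, the rule is given as an example for three conditions, and a predicted risk is not an observed one. It is a reason to give the fivefold range and SD 0.8 little weight.

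A reader might go further and infer that the primary hazard ratio will be biased toward 1 and its standard error overstated. The documents do not support that. It would require that the strata are in fact omitted and that they are clearly prognostic, and the protocol says neither. Even then, the shift in the hazard ratio is non-collapsibility, which vanishes at HR 1. The standard error is too large only against the reduced sampling variation; the reported value hardly changes when strata are added.

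**Conclusion.** The point holds as a minor one. The protocol restricts the randomisation and does not tie its primary ITT-1 model to that restriction. If the strata are omitted and prognostic, the cost is power: nothing to about 2 points with weak strata, about 3 to 5 points with a threefold hazard range, and roughly 7 to 12 points only with very strong strata. The hazard ratio then answers a population-average question and lies slightly nearer 1 than the within-stratum one.

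Validity is not at stake, since there is no confounding and no inflation of type I error. The sizes rest on assumed strata, event shares of about 38% to 70%, and a hazard ratio of 0.90 to 0.915, none of which the protocol gives. What remains is a real gain available without new data, together with clarity on which hazard ratio is primary.

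**What to change.** In the Statistical analysis section, state that the proportional hazard model for the primary ITT-1 comparison is stratified by, or adjusted for, the sociodemographic strata used in the allocation. Say that sparse strata will be merged, by a rule set before the outcome data are examined. Report the unstratified hazard ratio as a supporting result. If an analysis plan already specifies this, a cross-reference is enough.

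The cost is one sentence. Strata used for allocation are known for everyone randomised, so no new data are needed. The only practical burden is deciding how sparse strata are combined.
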